#### Secondary Outcome Analyses

Secondary analysis will be performed by repeated measures analysis of covariance with and without adjustment for baseline characteristics. The analyses used for secondary outcome measures will include unpaired t-test (serum ferritin, Key's index), Mann-Whitney U-test (DPO dosage) and chi square test (adverse drug reactions).

Categorical baseline characteristics (e.g. sex, race, comorbid illnesses, etc.) will be summarized with the number and percent of subjects in each treatment group with the characteristic. Quantitative characteristics (e.g., age and weight) will be summarized by mean and standard deviation or median [interquartile range], depending on data distribution. The number and percent of subjects who are randomised, treated with randomized Study Drug, require intervention, prematurely discontinue, and complete the study will be summarized. Fisher's exact test or the Chi-square test will be used to assess treatment group differences in the proportions of subjects who require intervention and who complete the study. The number and percent of subjects will be summarised for each reason for premature discontinuation.

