### Study design

The study is a prospective, open-label, randomised controlled trial. Patients will be randomised to one of two treatment groups in equal proportion (Figure 1). To ensure adequate concealment of allocation, the randomisation will be performed using sequentially numbered, opaque, sealed envelopes, stratified for the presence or absence of a TSAT ≤ 20%. The sequence of interventions was obtained from a computer-generated random number list in permuted blocks provided through the Australasian Kidney Trials (AKTN) network.

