### Procedures

Patients will take 2 tablets (HIP or ferrous sulphate) nocte for a period of 6 months. They will be instructed to take their study medications on an empty stomach and at least 2 hours apart from phosphate binder ingestion. At the time of inclusion in the study, demographic and clinical data will be recorded. All patients will be allowed their usual diet during the study period. DPO dosages will modified according to unit protocols, based on haemoglobin level. Full blood counts will be measured monthly, as per usual clinical practice. Iron studies will be measured every 2 months, as usual clinical practice. Patients will receive a medical review by their nephrologists every 2 months, as per usual clinical practice. No other procedure will be undertaken and all other care (including blood tests) will be provided according to standard unit protocols. Figure 2 outlines the trial schedule.

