### Sample size calculations

Prospective power calculations indicate that the study will have adequate statistical power (80% probability) to detect a clinically significant increase in TSAT of 7%, assuming α = 0.05 and a population standard deviation of 8%, if 44 patients were recruited in the study (22 in each group). Allowing for a 15% drop-out rate over 6 months using the adjustment formula of 1/[1 - drop-out rate] ^2^, we aim to recruit a total of 60 patients (30 in each group). We anticipate that a recruitment period of 18 months will be required. The assumptions for these power calculations were based on a previous randomised controlled trial of oral versus intravenous iron supplementation in PD patients [8], in which the baseline values were 107 ± 3 g/L for haemoglobin, 24.2 ± 1.7% for transferrin saturation and 323 ± 46 μg/L for serum ferritin concentration. Based on these assumptions, we estimate the power of the study for secondary outcome measures to be 77% for serum ferritin (δ 150 μg/mL, σ 180 μg/mL), 62% for haemoglobin (δ 7 g/L, σ 10 g/L), 22% for DPO divided by haemoglobin (δ 0.00075 μg.L/kg.g/week, σ 0.002 μg.L/kg.g/week) and 93% for the occurrence of gastrointestinal events (HIP 8% vs ferrous sulphate 46%).

The assumptions used for the power calculations are conservative and based on our previous study in 28 PD patients [22] and that of Nissenson et al in 37 haemodialysis patients ^1^. Because of power considerations and the relatively short duration of the study, no interim analysis is planned.

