### Statistical analysis

#### Primary Outcome Analyses

Differences between the intervention and control groups with respect to the primary outcome measure (TSAT level at 6 months) will be measured by comparison of the mean TSAT in each group, adjusted for baseline values (analysis of covariance). Data will be analysed on an intention to treat basis. For patients withdrawing before the end of the 6 month study, their TSAT at the time of withdrawal will be taken as their final haemoglobin.

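### Ferritin, Key's index and DPO dosage each have two unranked analyses, and the named tests leave out the outcome's baseline value and the randomisation stratum

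*Protocol article*

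**What the plan says.** Under Outcome measures, the protocol article defines each secondary outcome as a between-group difference at 6 months. The outcomes are ferritin, haemoglobin, DPO dosage, Key's index and adverse events.

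Secondary Outcome Analyses then makes two statements in succession. One is general and names a single model for everything: "Secondary analysis will be performed by repeated measures analysis of covariance with and without adjustment for baseline characteristics".

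The other assigns simple two-sample tests to individual outcomes and mentions no covariate. It begins: "The analyses used for secondary outcome measures will include unpaired t-test (serum ferritin, Key's index"). It goes on to give DPO dosage a Mann-Whitney test and adverse drug reactions a chi-square test.

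The section does not say how the two statements relate. Haemoglobin is not in the list of named tests.

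For comparison, the primary outcome is "adjusted for baseline values (analysis of covariance"). Under Study design, randomisation is "stratified for the presence or absence of a TSAT ≤ 20" (per cent). No other stratification factor is named.

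**The concern.** Read literally, ferritin, Key's index and DPO dosage can each yield three results: a repeated-measures ANCOVA with adjustment, the same model without it, and a two-sample test that uses no covariate. None is designated. The methods need not estimate the same quantity either. A repeated-measures group effect may average over visits, whereas the outcome is defined at month 6. In an open-label trial, leaving the choice open means the more favourable result could be the one emphasised.

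The second issue is efficiency. The two-sample tests discard the baseline value of the outcome, which the plan already uses for TSAT, and the factor on which randomisation was stratified. By the plan's own figures, ferritin and haemoglobin fall below 80% power, so precision available from data already collected is worth having.

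**Working it through.** **Inputs from Sample size calculations.** The evaluable number is fixed by "if 44 patients were recruited in the study (22 in each group"), and the error rate by "assuming α = 0.05 and a population standard deviation of 8" (per cent, for TSAT). Sidedness is not stated; two-sided reproduces the plan's figures. The differences and SDs are:

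- ferritin: δ 150, σ 180
- haemoglobin: δ 7, σ 10 g/L
- Key's index: δ 0.00075, σ 0.002

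**Input assumed.** The correlation ρ between baseline and 6-month values is not in the document. It is taken as 0.3, 0.5 and 0.7.

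**Step 1: reproduce the plan's figures.** For an unpaired t-test with n = 22 per group, the noncentrality is (δ/σ)·√(n/2) = (δ/σ)·√11, with 2n − 2 = 42 degrees of freedom and a two-sided critical value of 2.018.

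| Outcome | δ/σ | Noncentrality | Power | Stated |
|---|---|---|---|---|
| Ferritin | 0.833 | 2.764 | 77.0% | 77% |
| Haemoglobin | 0.700 | 2.322 | 62.1% | 62% |
| Key's index | 0.375 | 1.244 | 22.9% | 22% |

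All three agree to within a percentage point. With 30 per group the same test gives 88.8%, 76.0% and 29.8%, which do not match. The stated powers are therefore those of an unadjusted t-test at 22 per group, for haemoglobin as well as for the two outcomes to which the t-test is assigned.

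**Step 2: adjust for the outcome's baseline value.** In an ANCOVA with one covariate the residual SD is σ·√(1 − ρ²), with 2n − 3 = 41 degrees of freedom and a critical value of 2.020. For ferritin at ρ = 0.5, the residual SD is 180·√0.75 = 155.9, the noncentrality is (150/155.9)·√11 = 3.19, and power is 87.6%.

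| Outcome | t-test | ρ = 0 | ρ = 0.3 | ρ = 0.5 | ρ = 0.7 |
|---|---|---|---|---|---|
| Ferritin | 77.0% | 77.0% | 80.8% | 87.6% | 96.5% |
| Haemoglobin | 62.1% | 62.1% | 66.1% | 74.5% | 88.8% |
| Key's index | 22.9% | 22.9% | 24.7% | 28.9% | 39.8% |

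The degree of freedom spent on the covariate costs less than 0.1 percentage point, as the ρ = 0 column shows.

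**What cannot be computed.** No figure in the document allows a gain from adjusting for the TSAT stratum or for centre to be estimated. No SD or difference is given for DPO dosage itself, so no power can be calculated for it.

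**The case against.** The strongest reply is that the plan does not ignore baseline. The sentence immediately before the list of tests calls for ANCOVA with baseline adjustment as one version, so power is lost only if the two-sample tests are definitive, which the text does not say. This stands, and the power figures are conditional on it. It does not settle the matter, because the phrase baseline characteristics need not mean the outcome's own baseline value, and the adjusted version has no precedence over the others.

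Four stronger readings are tempting and are not supported:

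- *Haemoglobin has no analysis.* The general ANCOVA sentence covers it, and the list of tests is introduced as non-exhaustive. What is missing is only a designated analysis.
- *The plan loses power by omitting centre.* Centre is not a stated stratification factor. The one reason to consider it is that "DPO dosages will modified according to unit protocols, based on haemoglobin level", and no gain can be calculated.
- *A t-test for Key's index is wrong because DPO dosage gets a rank test.* Key's index is DPO dosage divided by haemoglobin, so the different treatment is unexplained. But the document gives no distributional data. Its power statement expresses the index per kilogram, while it does not say whether DPO dosage is weight-adjusted. This argues for consistent treatment and shows no error.
- *The unadjusted tests are biased.* Under randomisation they are valid; chance imbalance affects precision.

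The correlation could also be lower than assumed. DPO titration to haemoglobin may weaken the link between baseline and month 6, and the entry limit on ferritin narrows its baseline range. Below ρ = 0.3 the gain is under about 4 points. The calculation is on the raw scale, so it does not carry over exactly to a log or rank analysis.

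**Conclusion.** The point holds in this form. The section commits to more than one analysis for ferritin, Key's index and DPO dosage without saying which decides the 6-month comparison, and the named tests omit the outcome's baseline and the randomisation stratum. That is a defect in the stated text, not detail left to a fuller document.

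The cost in power is conditional on the unadjusted tests being definitive and on the assumed correlation. Over ρ = 0.3 to 0.7 the gain forgone is about 4 to 20 points for ferritin, 4 to 27 for haemoglobin and 2 to 17 for Key's index, falling to none at ρ = 0. Key's index stays underpowered across the whole range. The primary analysis is unaffected. The change should be made because it costs almost nothing, but the existing tests are not invalid.

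**What to change.** For each continuous secondary outcome, including haemoglobin, name one definitive month-6 analysis. This can be an ANCOVA or the repeated-measures model with a month-6 contrast, adjusted for the outcome's own baseline value and the TSAT stratum (≤ 20% or above). Treat DPO dosage and Key's index in the same way, on a log scale or with a rank-based ANCOVA if they prove skewed. Label the t-test, the Mann-Whitney test and the unadjusted ANCOVA as sensitivity analyses. Adjustment for centre is optional.

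The cost is wording and two degrees of freedom per model (baseline value and a two-level stratum), plus two more if the three centres are included. Iron studies and blood counts are already scheduled, so no new data or visits are needed.

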## Discussion

This investigator-initiated multicentre Australian study has been designed to provide evidence to help nephrologists and their CKD patients better determine whether HIP (Proferrin^®^ES) will more effectively augment iron stores in ESP-treated PD patients than conventional oral iron supplementation. Concomitant iron supplementation is required in as many as 90% of ESP-treated individuals [5]. However, the optimal means of administering iron to PD patients remains unclear: administration of intravenous iron is logistically difficult and costly, while conventional oral iron supplementation is also associated with poor compliance, gastrointestinal side effects and suboptimal GI absorption of iron [9]. Thus, the development of an oral iron supplement which is able to safely, cheaply and more effectively maintain iron stores and haemoglobin levels in ESP-treated PD patients would fulfil a currently unmet clinical need.

The multicentre nature of this trial will greatly enhance its generalisability. Moreover, the trial sample size has been carefully and prospectively calculated using a minimum clinically important difference in TSAT of 7% and realistic estimates of trial drop-out and non-compliance rates to minimise the risk of a type 2 statistical error.

It is hoped that results will be available in 2010. Demonstration of a significant improvement in iron stores with oral HIP therapy will provide clinicians with an important new therapy for effectively combating inadequate iron stores in PD patients.

## List of abbreviations

ANCOVA: Analysis of covariance; AKTN: Australasian Kidney Trials Network; BSE: Bovine spongiform encephalopathy; CKD: Chronic kidney disease; CTN: Clinical trials notification; DPO: Darbepoetin alpha; EPO: Erythropoietin; ESA: Erythropoiesis stimulating protein; ESKD: End-stage kidney disease; Hct: Haematocrit; HEMATOCRIT: **HEM**e iron polypeptide **A**gainst **T**reatment with **O**ral **C**ontrolled **R**elease **I**ron **T**ablets; Hgb: Haemoglobin; HIP: Heme iron polypeptide; HLGT: High level group term; IVRS: Interactive voice response system; MedDRA: Medical dictionary for regulatory activities; PD: Peritoneal dialysis; SOC: System organ class; TGA: Therapeutic Goods Administration; TSAT: Transferrin saturation.

